#### Data analysis

First, an exploratory data analysis will be performed to determine the distributions of the different variables and evaluate their normality using the Kolmogorov–Smirnov test, kurtosis analysis and skewness. Measures of central tendency and dispersion will be calculated, as well as percentage distributions. Subsequently, a bivariate analysis will be performed using the Chi-square test for comparison of qualitative variables, and Student's *t*-test for independent groups for quantitative variables. In case of non-parametric distribution, the Mann–Whitney *U* test will be performed.

In addition, repeated measures ANOVA will be used to determine intra-group progression of the different variables throughout the monitoring period, to evaluate the time effect.

Finally, a multivariate regression model will be constructed using Cox regression to evaluate the primary endpoints (cure and adherence), with follow-up periods as time adjusted for the variables found to have a significant association on bivariate analysis. The raw and adjusted hazard ratio for treatment failure and non-adherence will be estimated.

All the analyses will be performed by intention to treat (ITT) and by multiple imputation using the monotonic approach if missing data show a monotonic pattern; otherwise, the fully conditional specification will be used. Patients will be analysed in the group to which they will be initially allocated, regardless of whether they finally receive the randomized intervention.

All analyses will be done with estimation of 95% confidence intervals.

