##### Endpoints and measures

The cure rate and adherence to treatment will be the primary endpoints. To assess cure, HCV viral load will be determined 8–12 weeks after the end of treatment. Patient adherence to treatment will be evaluated using the AIDS Clinical Trials Group method. By this method, patients are inquired about medications not taken in a period of four days prior to the interview: % adherence = (total galenic units prescribed for that period—total units not taken) / total galenic units prescribed for that period [40]. The cut point for this measure has been set to 95%, as the best threshold for a predictive positive virologic response in patients with HIV [41]. A record will also be kept of whether the patient needed to use a pillbox to ensure medication intake and/or required monitoring by the family or the mental health unit to guarantee the correct use of the treatment.

Secondary endpoints include sociodemographic and clinical data and data related to the healthcare process. Other variables in relation to the patient include changes in daily functioning as assessed using the Life Skill Profile (LSP) [42]; negative symptoms, measured on the Positive and Negative Syndrome Scale (PANSS) [43]; and changes in quality of life, measured with the Euroqol5D Health Questionnaire [44], all of them in their Spanish version (See Table 1). These questionnaires will be administered by an evaluator (psychologist or nurse) trained for it and blind to the experimental condition assigned to each patient.

**Table 1 Tab1:** Psychometric characteristics of the instruments included

Questionnaire	Domain (s)	Psychometric properties
**Life Skill Profile (LSP)** [42]	Self-care	Concurrent validity, this scale was compared with the social behaviour schedule SBS: 0.56 Interrater reliability *r* = 0.62, and internal consistency α = 0.82
	Interpersonal social behaviour	Concurrent validity, this scale was compared with the social behaviour schedule SBS: 0.54 Interrater reliability *r* = 0.69, and internal consistency α = 0.77
	Communication and social contact	Concurrent validity, this scale was compared with the social behaviour schedule SBS: 0.63 Interrater reliability *r* = 0.86, and internal consistency α = 0.86
	Non-personal social behaviour	Concurrent validity, this scale was compared with the social behaviour schedule SBS: 0.36 Interrater reliability *r* = 0.76, and internal consistency α = 0.78

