Regarding healthcare process indicators, the number of previously detected but untreated cases, detection rate after screening the SMD population, percentage of detected cases referred to the digestive service, and delay time until first consultation with the specialist will also be recorded. In addition, scheduled and unscheduled visits led by the monitoring team and number of calls made and received by this team will be recorded. Regarding hepatitis, case classification by genotype and treatment administered will also be recorded. In addition, the prevalence of undiagnosed HCV infection and diagnosed but untreated HCV infection in SMD patients will also be estimated. Finally, a comparison of daily life functioning, occurrence of symptoms, quality of life, and frequency of adverse events during active infection and once cured will be performed.

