Likewise, there is consistent evidence that patients with SMD often have treatment adherence problems [52, 53]. This population of patients also show difficulties in navigating through complex clinical pathways that imply attending several appointments in various health services at different times, probably due to their impaired executive function [54, 55]. In the case of HCV, the clinical pathway involves, but not limited to, visits to the services of mental health, microbiology, primary care, digestive medicine, and hospital pharmacy. When the patient has adherence problems, it may be necessary that they are accompanied throughout complex processes including follow-up visits related to physical health problems. These patients are frequently accompanied by nurses [56, 57]. For this randomized controlled trial, an approach tailored to patient’s needs and context will be adopted to maximize treatment adherence and, as far as possible, ensure resolution of HCV infection. Once the study is completed, this model of care will be offered to the rest of patients of the Mental Health Service Unit of the University Regional Hospital of Málaga. If the trial proves to be effective, this model could be easily applied at other Mental Health services. Moreover, the study is designed from a pragmatic approach, with no extraordinary modifications of daily practice, except for the implementation of an NNP. Thus, the intervention will be implemented by the Mental Health Unit staff itself. If results are satisfactory, the sustainability of the model is guaranteed and its generalization to other Mental Health Units of the Public Health Care System is easily achievable in Spain. Furthermore, mental health services are well-positioned to lead a more active role in the treatment of HCV and engage patients in the treatment process [49].

A secondary contribution of this study is that it will provide data on the prevalence of HCV symptoms such as apathy, anhedonia, tiredness (Negative symptoms scale, PANSS), which are commonly attributed to schizophrenia or to the side effects of usual pharmacological treatments such as antipsychotics or mood stabilizers. During the study, all these symptoms will be recorded at baseline and once infection has been cured. Consequently, it is a unique opportunity to assess the occurrence of symptoms once HCV infection is resolved. If these symptoms persist after HCV infection is controlled, a psychotic aetiology will be confirmed.

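### LSP, PANSS negative and EQ-5D have no baseline-adjusted or arm-by-time comparison, and symptoms that persist after cure cannot confirm a psychotic aetiology

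*Protocol article*

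**What the plan says.** The Endpoints and measures section lists three patient scales as secondary endpoints: "changes in daily functioning as assessed using the Life Skill Profile (LSP"), "negative symptoms, measured on the Positive and Negative Syndrome Scale (PANSS"), and change in quality of life on the EQ-5D.

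The Data analysis section offers two analyses that can apply to them:

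- Between arms: Student's t "test for independent groups for quantitative variables", replaced by Mann-Whitney if the distribution is not normal. No baseline term is mentioned.
- Over time, introduced as an addition: "repeated measures ANOVA will be used to determine intra-group progression of the different variables throughout the monitoring period, to evaluate the time effect".

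The only adjusted model is a regression "using Cox regression to evaluate the primary endpoints (cure and adherence"), so it does not reach the scales. All analyses are to follow intention to treat and to carry 95% confidence intervals.

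Endpoints and measures also plans "a comparison of daily life functioning, occurrence of symptoms, quality of life, and frequency of adverse events during active infection and once cured", with no comparator named. The Discussion describes the symptoms at issue (apathy, anhedonia, tiredness) as "commonly attributed to schizophrenia or to the side effects of usual pharmacological treatments such as antipsychotics or mood stabilizers". Three sentences later it says: "If these symptoms persist after HCV infection is controlled, a psychotic aetiology will be confirmed".

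**The concern.** There are two separate problems.

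The first is the analysis of the scales. The one longitudinal model is directed at time within each arm. A time effect within an arm mixes any effect of the programme with time trend, regression to the mean, concurrent psychiatric care and repeated assessment, and it makes no use of randomisation. The term that would carry the treatment comparison, arm-by-time, is not named. The between-arm test that is named has no baseline adjustment, although baseline scores are collected. What is at stake is precision on the secondary outcomes, and whether the longitudinal output answers the trial's question.

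The second is an inference fixed in advance. Clearing the virus removes one candidate cause of a symptom. If the symptom remains, that does not tell the other candidates apart, and the article names one of them itself. This matters because the Background argues that symptoms in these patients are seldom attributed to a physical illness. A result reported as confirming a psychotic cause would favour the psychiatric explanation without evidence for it.

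**Working it through.** **The plan's own figure.** No sample size is given for the scales. The only planned size, in the Sample section, is for adherence: 80% versus 65%, alpha 0.05, beta 20%. Assuming a two-sided test, 1:1 allocation, pooled variance and no continuity correction:

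n per arm = [1.96·√(2·0.725·0.275) + 0.8416·√(0.80·0.20 + 0.65·0.35)]² / 0.15² = (1.2377 + 0.5239)² / 0.0225 ≈ 137.9, rounded up to 138.

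The total is 276, which matches. It is used below only as an arm size for illustration.

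**Precision of the between-arm test.** Let r be the correlation between baseline and follow-up score, with equal variances scaled to 1. The documents give no r, so 0.5 to 0.7 is assumed. The per-patient residual variances are:

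- follow-up-score t-test: 1
- change-score t-test: 2(1 − r)
- baseline-adjusted ANCOVA: 1 − r²

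The standard-error ratio of ANCOVA to the follow-up-score test is √(1 − r²). The ratio to the change-score test is √[(1 − r²) / (2(1 − r))] = √[(1 + r)/2].

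| r | ratio to follow-up test | SE cut | ratio to change-score test | SE cut |
|---|---|---|---|---|
| 0.5 | √0.75 = 0.866 | 13% | √0.75 = 0.866 | 13% |
| 0.7 | √0.51 = 0.714 | 29% | √0.85 = 0.922 | 8% |

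In terms of power, with 138 per arm and an assumed between-arm difference of 0.3 SD:

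| r | follow-up test | change-score test | ANCOVA |
|---|---|---|---|
| 0.3 | 70% | 56% | 74% |
| 0.5 | 70% | 70% | 82% |
| 0.7 | 70% | 90% | 94% |

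ANCOVA has the highest power in every row. The margin depends on r and on which unadjusted test is meant.

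**The aetiology sentence.** No arithmetic applies, so the statements are set side by side.

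- The Background says neuroleptics and stabilizers, which these patients generally take, cause dejection, tiredness and anhedonia.
- The Discussion says the symptoms in question are attributed to schizophrenia or to those drugs' side effects.
- The Introduction includes bipolar disorder and major depression within severe mental disorder.
- The Discussion then concludes that persistence after HCV control confirms a psychotic cause.

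The first three statements leave at least two other explanations open after cure: drug effects, and a mental disorder that is not psychotic. Nothing in the design separates these from a psychotic cause, so the fourth statement does not follow.

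**The case against.** The strongest reply is that a randomised comparison of the scales is planned. The independent-groups test is valid, it follows intention to treat, and the repeated measures ANOVA is only an addition with a stated, limited purpose. This stands. A reader might infer that significance in one arm but not the other will be taken as a treatment effect. If both arms changed equally and each within-arm test had power p, exactly one would be significant with probability 2p(1 − p), which is 50% at p = 0.5 and 32% at p = 0.8. The documents never say that the time effects will be read this way, so these figures describe an error to which the plan does not commit.

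A reader might also infer that baseline is ignored altogether. That is not established. LSP and EQ-5D are defined as changes, so baseline may enter by subtraction. The gain from adjustment is then the smaller 8-13%. PANSS negative symptoms are not defined as a change.

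A third tempting reading is that before-after improvement is to be taken as proof of aetiology, so that regression to the mean or contact time would mislead. The text says the opposite: it draws its conclusion from persistence, which those two mechanisms would not normally produce. The fault is that other causes remain, not that a change is spurious.

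Finally, model terms for secondary scales are often left to an analysis plan, and none is shown. This limits the weight of the first problem. It does not remove it, because the article itself names the longitudinal model and directs it at the time effect. The aetiology sentence is a single Discussion remark that governs no endpoint or decision, but it is still wrong as written.

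**Conclusion.** Both problems hold, at moderate weight. The secondary scales are compared between arms by a valid but unadjusted test, and followed over time by a model that does not estimate the effect of the programme. The cost is precision: roughly 13-29% of the standard error if follow-up scores are tested, and roughly 8-13% if change scores are. These ranges rest on an assumed baseline correlation of 0.5 to 0.7, equal variances and a t-test rather than Mann-Whitney. The power figures also assume 138 per arm and a 0.3 SD difference. No bias in the planned between-arm test is shown, and the primary endpoints are not affected.

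The aetiology statement is an unsupported inference on the article's own text and rests on no numerical assumption.

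**What to change.** - Analyse LSP, PANSS negative and EQ-5D by ANCOVA, or by a mixed model with arm, time and arm-by-time, adjusted for the baseline score in either case. Report the between-arm difference with its 95% confidence interval.
- Label the within-arm time effects and the comparison of active infection with the cured state as descriptive.
- Replace the Discussion sentence on psychotic aetiology with one saying that persistence shows only that clearing the virus did not resolve the symptoms.

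The cost is a few lines of analysis text and one sentence of the Discussion. The baseline and follow-up scores are already to be collected, so no new data, visits or patients are needed.

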##### Sample

As far as we know, there are no comparative studies assessing adherence of SMD patients to HCV treatment. For this reason, adherence to lifelong treatments such as oral antidiabetics in patients with schizophrenia has been taken as a reference. Based on data from Kreyenbuhl et al. [38], in which differences in adherence of patients with schizophrenia reached 10%, with an alpha of 0.05, a beta of 20%, and raising the threshold of differences to 15% because, unlike oral antidiabetics, it is a temporary treatment, the needed sample would be 276, assuming that adherence will be 80% in the intervention group and 65% in the control group. This sample will be increased by 15% to cover losses. Additionally, we considered the adherence threshold obtained by Ho et al. in their pilot non-controlled study for patients with HCV and psychiatric disorders, [39] with the same estimation parameters, resulting in a similar sample size.

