#### Interventions

In this study, a navigation program led by mental health nurses and auxiliary nurse technicians from a mental health unit will be implemented.

The control group will receive the standard of care. Patients in this group will be directly referred to their family physician with a report showing a positive HCV and viral load test for prescription of the standard treatment established by the Andalusian Health System. Standard management involves referral to the gastroenterologist, with a significant delay. Generally, the gastroenterologist prescribes a series of tests to confirm diagnosis. These tests will be performed in other units, for which previous appointment is required. Once test results become available, the patient will have another consultation with the gastroenterologist, who will finally establish a diagnosis and prescribe the treatment. The prescribed drug will be dispensed at the hospital pharmacy once a month until the treatment is completed, and cure is confirmed. The last phase of the treatment involves a final visit with the gastroenterologist to confirm that the viral load has disappeared according to a laboratory test.

In the intervention group, patients will be accompanied throughout the evaluation and treatment process until they are fully cured. The details of the intervention are described following the template for intervention description and replication (TIDiER). Follow-up will include a simplification of the clinical pathway of treatment. This way, the mental health service refers the patient to a first visit with the gastroenterologist. To guarantee compliance, all patients will be accompanied to that appointment either by a competent available family caregiver or by a member of the NNP team.

In the first visit, the gastroenterologist will perform a liver ultrasound and determine the most appropriate treatment for each patient. In the same visit, the patient will receive the prescribed pharmacological treatment, which will be dispensed at the hospital pharmacy. Thus, the patient obtains a final diagnosis and his pharmacological treatment the same day following a single-step clinical pathway.

The mental health nurse team will subsequently arrange for the analysis of the genotype of the virus in the mental health service, if necessary.

The intervention is based on an *ad-hoc* decision algorithm developed by all the healthcare services involved (See Fig. 1).

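### The only adjusted model for cure and adherence is a Cox regression, although both are yes/no results read at scheduled visits and the sample size compares two proportions

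*Protocol article*

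**What the plan says.** All references are to the protocol article.

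- **Endpoints and measures** defines cure by one laboratory reading: "HCV viral load will be determined 8–12 weeks after the end of treatment". Adherence is a four-day recall percentage with a cut point of 95%.
- **Monitoring** places an evaluation of all patients, including adherence, at the end of the 8–12 week treatment, and a last reading of all variables six months after treatment starts. The Abstract also times follow-up from antiviral treatment, at three and six months.
- **Sample** sizes the trial on adherence "with an alpha of 0.05, a beta of 20"%: "the needed sample would be 276, assuming that adherence will be 80% in the intervention group and 65% in the control group".
- **Data analysis** plans a chi-square test for qualitative variables. For the primary endpoints it then says that "a multivariate regression model will be constructed using Cox regression to evaluate the primary endpoints (cure and adherence), with follow-up periods as time", adjusted for covariates significant in the bivariate step. The output is fixed too: "The raw and adjusted hazard ratio for treatment failure and non-adherence will be estimated". All analyses are to be by intention to treat. No time origin is named.
- **Interventions** describes unequal routes to treatment. For controls, "Standard management involves referral to the gastroenterologist, with a significant delay", followed by tests and a second consultation. Intervention patients receive diagnosis and drug on the day of the first specialist visit.

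**The concern.** A Cox model compares when events happen among people still at risk. Here nothing is observed to happen at a time. A patient who is not cured, or not adherent, is found to be so on the day of the test, and patients with good results are censored on that same kind of day. The time variable therefore carries the visit calendar and no information about outcome.

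Two things are at stake. First, the adjusted analysis may have less power than the trial was sized for. Second, if the clock starts before treatment, the calendar differs between arms because of the intervention itself. Intervention failures would then be counted while controls not yet tested sit in the risk set as if free of failure.

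**Working it through.** **Inputs.** Adherence 80% vs 65%, so failure 20% vs 35%; alpha 0.05; power 80%; N = 276 (all from Sample). Two assumptions: a two-sided test and 1:1 allocation, neither of which is stated. Both are supported by the fact that they reproduce 276. The article gives no cure rates, so the figures below use the adherence rates.

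**1. The plan's own figure.** Two proportions, pooled variance under the null, mean proportion 0.725:

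n per arm = [1.960 × √(2 × 0.725 × 0.275) + 0.842 × √(0.80 × 0.20 + 0.65 × 0.35)]² / 0.15² = [1.238 + 0.524]² / 0.0225 ≈ 138, so N = 276.

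This matches exactly. The 276, and its 80% power, belong to a comparison of proportions. ("This sample will be increased by 15% to cover losses"; that does not affect this point.)

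**2. Everyone read at one identical time.** Expected failures are 138 × 0.20 = 27.6 and 138 × 0.35 = 48.3.

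- log risk ratio: ln(0.20/0.35) = −0.560, ratio 0.571.
- Cox standard error, Breslow ties: √(1/27.6 + 1/48.3) = 0.239.
- True (binomial) standard error: √(0.80/27.6 + 0.65/48.3) = 0.206.
- Power with Breslow: Φ[(0.560 − 1.960 × 0.239)/0.206] ≈ Φ(0.45) = 67%.

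Simulation agrees: chi-square about 80%, Cox–Breslow 68%, Cox–Efron 80%. The median hazard ratio is 0.57 under Breslow and 0.52 under Efron on the same data. With no true difference, Breslow rejects in about 2% of trials instead of 5%.

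**3. Same calendar in both arms, dates spread (assumed SD 0.5 to 4 weeks).** Chi-square stays at about 80%. Cox gives about 65% under either tie rule (simulated values 63–67%). The Efron advantage disappears once dates are no longer identical.

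**4. Controls read later.** A case that can be done by hand: all intervention patients are read at one visit, and a share q of controls only at a later one. At the first visit 138 per arm are at risk; failures are 27.6 and 48.3 × (1 − q). At the later visit only controls remain, so it adds nothing. The Breslow hazard ratio is

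HR = 27.6 / [48.3 × (1 − q)] = 0.571 / (1 − q).

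| q | HR |
|---|---|
| 0 | 0.57 |
| 0.20 | 0.71 |
| 0.50 | 1.14 |
| 0.75 | 2.29 |

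It passes 1 at q = 0.43, although true failure is still 20% vs 35%.

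With continuous test dates, the simulated median HR is as follows. Delay and spread are both assumed, because the article gives neither.

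| Control delay | SD 4 weeks | SD 8 weeks | Uniform over 5–7 months |
|---|---|---|---|
| 2 weeks | about 0.9 | about 0.7 | 1.3–1.4 |
| 4 weeks / 1 month | about 1.4 | about 0.9 | about 3.3 |
| 8 weeks | about 4 | about 1.5 | not used |

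Chi-square keeps about 80% power for the intervention throughout. With no true difference (27.5% in both arms), SD 4 weeks and a 4-week delay, the HR is about 2.4–2.5, and Cox finds falsely against the intervention in about 95% of simulated trials.

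**The case against.** **A valid test is already planned.** The chi-square test, by intention to treat, applies to both endpoints and has the power the trial was sized for. This stands, so the trial's stated 80% power is not lost. It does not repair the hazard ratios or supply an adjusted estimate. The text also does not say which result prevails if the two disagree.

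**Power need not fall at equal follow-up.** This stands for one case: identical times for all patients with Efron ties. Tie handling is ordinary analysis-plan content and its absence is no fault. Real visit dates spread, however, and both rules then lose about 13–15 points.

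**The hazard ratio is not meaningless.** At one common time the Breslow value equals the risk ratio (0.571), and its test is conservative. That also stands, but only for that case.

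**The reversal needs a clock the article does not set.** A reader might infer that the plan will turn a benefit into apparent harm. The article does not support that. The Abstract and Monitoring time visits from treatment. With that origin the pre-treatment delay drops out for treated patients. But patients who never start treatment then have no origin, although the plan promises to analyse everyone as allocated. Randomisation remains a possible reading, and under it the direction of the bias is firm while its size is not: a 2-week delay gives anything from about 0.7 to 1.4 across the spreads tried.

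**Delay to first consultation.** The article says that "delay time until first consultation with the specialist will also be recorded". A reader might infer that it will be analysed by a test that drops patients who never attend. Data analysis assigns it no specific test and plans multiple imputation, so nothing is claimed here about it.

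**Conclusion.** The point holds for the adjusted model and the reported hazard ratios, and no further. Cox regression does not fit two endpoints that have no event time, and it departs from the two-proportion basis of the 276.

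At the plan's rates, the cost in power is about 10–15 points (roughly 65–70% against 80%) under Breslow ties or with dispersed dates. It is nil with Efron ties and identical times. This rests on 138 per arm and on using the adherence rates for both endpoints.

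The bias is conditional. It arises if time runs from randomisation, or if controls are tested later for another reason. With failure as the event, as the plan states, it then goes against the intervention. Its size cannot be fixed from the article. Over the assumed delays and spreads, the HR ranges from attenuated (0.7–0.9) to clearly reversed (about 3–4), against 0.57 with no delay.

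**What to change.** In Data analysis, replace Cox regression and hazard ratios for cure and adherence by:

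1. the risk difference and risk ratio with 95% confidence intervals, at one fixed assessment window named for each endpoint;
2. all randomised patients in the denominator, with a stated classification for those who never start treatment;
3. adjusted estimates from modified Poisson regression with robust variance, or from logistic regression with marginal standardisation.

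These match the basis of the 276 and do not depend on test dates within the window. At the plan's rates, unadjusted Wald power is 79.9% for logistic regression (simulated) and 77.5% for the risk ratio (log-binomial, analytic).

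The cost is a protocol text amendment and matching wording in the analysis plan. It needs no new data and no change in sample size.

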#### Monitoring

During the treatment period (8–12 weeks depending on the prescribed drug), actions will be taken to ensure correct treatment adherence. To such purpose, the mental health nurse will assess patient’s ability to comply with the treatment. In case of patient’s inability, the nurse will assess family’s commitment to supervise and remind the patient about drug intake. In both cases, the nurse will carry out an educational intervention to ensure that the patient and/or their family clearly understand treatment guidelines. This intervention is structured through a standardized care plan. In cases in which proper treatment use is not guaranteed, medication will be provided weekly by the monitoring team.

Upon completion of the 8–12 weeks treatment period, a final evaluation of all patients will be performed. The data collected in this evaluation visit include adherence to treatment, person responsible for treatment administration, occurrence of adverse effects or interactions, and number of visits and calls during the treatment period.

A third and final analysis of all study variables will be carried out six months after starting the treatment. Finally, disappearance of the viral load and, therefore, cure from HCV will be determined by a new blood test.

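### The covariate rule for the Cox model of cure and adherence is not limited to pre-randomisation variables, so the adjusted estimate can lose part of the programme's effect

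*Protocol article*

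**What the plan says.** The Data analysis section of the protocol article starts with group comparisons (chi-square, t or Mann–Whitney tests) and repeated-measures ANOVA. It then says that "a multivariate regression model will be constructed using Cox regression to evaluate the primary endpoints (cure and adherence"), and that this model is "adjusted for the variables found to have a significant association on bivariate analysis". Of the output it says: "The raw and adjusted hazard ratio for treatment failure and non-adherence will be estimated". Neither hazard ratio is named as the one on which the conclusion rests. The section gives no covariate list and no restriction by time of measurement. It does not say whether the bivariate association is with the outcome or with the randomised arm.

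Elsewhere the article lists data that arise after randomisation:

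- Endpoints and measures: "whether the patient needed to use a pillbox to ensure medication intake and/or required monitoring by the family or the mental health unit".
- Endpoints and measures, healthcare process indicators: "scheduled and unscheduled visits led by the monitoring team and number of calls made and received by this team will be recorded", and "delay time until first consultation with the specialist will also be recorded".
- Monitoring, collected at the end of treatment: "person responsible for treatment administration, occurrence of adverse effects or interactions, and number of visits and calls during the treatment period".

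**The concern.** The aim is the effect of the whole programme against standard care, analysed by intention to treat. Several of the recorded variables are ways in which the programme is meant to work. A variable on the path from arm to outcome is a mediator. A model that conditions on it no longer estimates the whole effect, only the part that does not pass through it.

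The rule as worded does not keep such variables out. If the screen is against the outcome, a mediator that matters for adherence tends to be selected. If the screen is against the arm, a variable that the programme changes tends to be selected. In either case the adjusted hazard ratio could show little effect for a programme that works as designed. With two estimates reported and neither declared primary, the reading of the trial would be settled after the data are seen.

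**Working it through.** **1. Which variables the rule admits.** Setting the sections side by side:

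| Recorded variable | What the programme does to it |
|---|---|
| Pillbox, supervised intake, person administering the drug | Monitoring: the nurse assesses ability, engages the family, and the team supplies medication weekly where proper use is not assured |
| Team visits and calls | Delivered by the monitoring team |
| Delay to first specialist consultation | Interventions: same-day single-step pathway, against a control pathway described as markedly delayed |

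The Monitoring section does not restate that its actions apply to the intervention arm only; I read it as part of the intervention. If the actions applied to both arms, the variables would still be post-randomisation but would differ less by arm.

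**2. The plan's own figure.** Inputs from the Sample section: 80% vs 65%, alpha 0.05 (taken as two-sided), power 80%. With the pooled two-proportion formula and mean proportion 0.725:

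n per arm = [1.960·√(2·0.725·0.275) + 0.842·√(0.65·0.35 + 0.80·0.20)]² / 0.15² = (1.238 + 0.524)² / 0.0225 ≈ 137.9, so 138 per arm and 276 in total.

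This matches the stated 276 exactly. That calculation is for an unadjusted contrast.

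**3. Effect of adjusting for one mediator.** Let M be a binary post-randomisation variable such as supervised intake. *Assumption:* M is present in 70% of the intervention arm and 20% of control. Model: P(adherent) = a + b·M + c·(arm). For an assumed share s of the effect passing through M:

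- b = 0.15·s / (0.70 − 0.20)
- c = 0.15·(1 − s)
- a = 0.65 − 0.20·b

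For s = 0.5, b = 0.15, c = 0.075 and a = 0.62. Control is then 0.62 + 0.03 = 0.65 and intervention 0.62 + 0.105 + 0.075 = 0.80, as planned. M enters if its chi-square p-value with adherence is below 0.05. Results from 1,500 simulated trials per row, 138 per arm, linear risk-difference model with robust standard errors:

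| Share via M | M selected | Mean effect after the rule | Power (unadjusted about 80%) |
|---|---|---|---|
| 25% | 68% | 11.6 points | 52% |
| 50% | 96% | 7.5 points | 24% |
| 75% | 99.7% | 3.6 points | 11% |
| 100% | 100% | about 0 | 6% |

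Repeat runs moved the power figures by no more than about two points; one gave 53% in the first row. With M in 80% vs 30%, power is 48%, 25%, 10% and 6%.

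**4. A less favourable case for the concern.** Supervision may go mainly to patients expected to adhere poorly. *Assumptions:* 40% of patients have low ability; supervision reaches 95% vs 30% of them by arm, and 15% vs 5% of the others; low-ability patients adhere in 30% of cases unsupervised; the others adhere in 85%, or 90% if supervised; the arm has no other effect.

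- Supervision adds 45 points in low-ability patients. Intervention: 0.4·0.7275 + 0.6·0.8575 = 0.8055. Control: 0.4·0.435 + 0.6·0.8525 = 0.6855. The difference is 12.0 points. The screen selects supervision in about 12% of runs, the mean effect becomes 11.7 points, and power goes from about 65% to 63%.
- Supervision adds 55 points. Arm rates are 0.8435 and 0.6975, a difference of 14.6 points. Supervision is selected in about 69% of runs, the mean effect becomes about 12.3 points, and power goes from about 85% to 68%.

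**The case against.** The strongest reply is that the main result survives. The unadjusted group comparison, on which the sample size rests, and the raw hazard ratio are both reported, and covariate selection affects neither. The article never calls the adjusted Cox model its primary model, and it does not say that process variables will be entered. All of this stands. It confines the harm to the adjusted estimate and to the open choice between the two. It does not remove the harm, because this is the model named for evaluating the primary endpoints and its covariate rule is stated outright. An SAP that followed the rule would carry it over.

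Three stronger readings are tempting and are not supported:

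- *That the screen is bound to pick the mediators and wipe out the effect.* The documents hold no data on how strongly these variables relate to cure or adherence. The pillbox and monitoring item is worded in terms of need, so supervised patients may be those at highest risk of non-adherence. That weakens the crude association, as step 4 shows. The fall to 6% power arises only where the whole effect is assumed to pass through one variable, so it is true by construction.
- *That the power loss is in proportion to the mediated share.* It is steeper: a quarter share already takes power from about 80% to just over 50%.
- *That data-driven selection by itself makes the confidence intervals invalid.* The article does not say that the screen uses the outcome. A check with baseline covariates only (3,000 runs, 10 covariates, 3 of them prognostic, outcome screen) gave a type I error of 5.1%, against 4.9% unadjusted. This is immaterial here.

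**Conclusion.** The point holds in a limited form. The rule permits, but does not require, adjustment for consequences of the programme in the model that evaluates both primary endpoints, and the article leaves open which hazard ratio decides. The adjusted estimate can therefore understate the programme's effect; the raw estimate is not affected.

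The size cannot be fixed from the documents. Under the assumptions shown, power for adherence runs from nearly unchanged, when supervision is directed at likely poor adherers, to about half or less of the planned 80% once one mediator carries half of the effect or more. These figures rest on assumed prevalences and mediated shares and on a risk-difference model in place of Cox regression. Cure was not simulated; the reasoning is the same for it, but no size is claimed.

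**What to change.** Replace the significance rule in the Data analysis section with the following:

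1. A fixed list of covariates measured before randomisation, chosen from those already collected: for example diagnosis type, baseline LSP, baseline PANSS negative score, use of drugs of abuse, family support, and mental health admissions in the last 12 months. Name the list before any outcome data are analysed. The trial is open and only outcome assessment is blinded, so a deadline tied to unblinding would not serve.
2. A statement that no variable measured after randomisation enters the model for cure or adherence.
3. A statement of which estimate, raw or adjusted, is primary for each endpoint.
4. Descriptive reporting by arm of the process variables (pillbox and supervision, person administering treatment, visits, calls, delay). Any mediation analysis should be separate and labelled as such.

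The cost is a wording change in the protocol and in the SAP, and the loss of freedom to choose covariates from the data. No new data and no change in sample size are needed: the planned 15-point contrast with 276 patients and 80% power stays as it is.
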